### Experimental design

This study protocol is based on the SPIRIT 2013 clinical trial protocol guidelines [52,53] (S1-S3 File) and follows a randomized, controlled, partially-blind design. This study will be conducted during a specially designed summer golf training camp, with all experimental procedures carried out within the camp period. During this time, all participants will follow the same diet, daily schedule, training, and competition routines to minimize dropout and external interference. The study consists of three main phases (Fig 2): familiarization with the experimental procedure, baseline testing, and the formal experiment. During the formal experiment, participants will be randomly assigned to one of the following three groups: (MF-Mu Group) Participants undergo a mental fatigue induction task followed by a music intervention; (MF-nMu Group) Participants undergo a mental fatigue induction task but do not receive a music intervention; (CON Group) Participants neither undergo a mental fatigue induction task nor receive a music intervention.

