**Fig 2 pone.0337905.g002:**
[figure not shown]
Overview of the experimental design.

Randomization of group allocation and participant order will be conducted using a random number table generator (www.randomizer.org), ensuring that no one can predict the group assignments before randomization. Participants will not be informed of the true purpose of the study; instead, they will be told that the study is part of a summer golf training camp and that they should perform their best during the skill testing phase. During the intervention, dedicated assistants will be responsible for inducing mental fatigue and administering the music intervention, but they will not be informed of the specific research objectives. During the golf skill testing and performance recording phase, testing assistants will be responsible only for recording test results and will not be aware of the participants’ group assignments. Data analysis will be conducted by researchers who only have access to anonymized data. Group assignment information will only be disclosed to the on-site medical team in case of participant health concerns. This design is conducive to blinding control. [54–56].

The total intervention duration is 45 minutes, consisting of 30 minutes of mental fatigue induction and 15 minutes of music intervention. Participants not undergoing mental fatigue induction will read some magazine leisurely, a common control in mental fatigue trials [57–59]. Those not receiving the music intervention will sit quietly and rest, a common control in music intervention trials [60–62], to control external factors and maintain consistent conditions. Immediately after the intervention, participants will complete golf skill testing, with the testing site located within a 2-minute walking distance from the intervention area. Performance outcomes include driving performance, iron shot performance, chipping performance, and putting performance. Golf skill test data will be collected on-site by assistant researchers and verified and signed off by a national-level referee to ensure validity.

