During the music intervention phase, participants will listen to 15 minutes of classical music to facilitate mental fatigue recovery. Research has shown that short-term listening to classical music can effectively alleviate mental fatigue [60,66–68]. Among classical music, Mozart’s compositions are particularly effective in cognitive function recovery, attention enhancement, emotional regulation, and mental fatigue relief due to their bright and optimistic style, pure and elegant melodies, and harmonious rhythms [69–71]. Therefore, This study selects Mozart’s Eine Kleine Nachtmusik as the intervention music [72], a piece that has been applied in previous mental fatigue recovery studies and has been validated as an effective intervention [66]. The intervention duration is set at 15 minutes, as multiple studies have confirmed this duration to be sufficient to produce recovery effects without causing additional cognitive load or auditory fatigue [66,73,74]. Based on research in the field of music therapy, the intervention volume should be maintained between 50–60 dBA [71,75–77]. The music will be played through a smartphone. Considering that the maximum volume of a smartphone is approximately 105–113 dBA [78], the standardized intervention volume was set at 50% of the maximum (52.5–56.5 dBA), with participants allowed to make slight adjustments to ensure listening comfort. Participants in the MF-Mu group will wear earphones and listen to the music for 15 minutes, while those in the MF-nMu and CON groups will wear earphones in the same environment but without audio, simply sitting at rest for 15 minutes. This experimental design effectively controls for non-musical factors, ensuring that the observed effects can be solely attributed to the music intervention.

The mental fatigue induction and music intervention will be conducted in the same classroom, with the room temperature maintained at 24°C, soft lighting, and no background noise. This study has chosen smartphones instead of computers as the experimental devices because listening to music via smartphones during non-hitting intervals in official golf competitions complies with golf regulations. Thus, using smartphones enhances the real-world applicability of the study’s conclusions in actual competition settings.

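### The design identifies classical music versus silent rest after a Stroop task, not an effect due solely to music, and only MF-Mu versus MF-nMu bears on it

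*Protocol article*

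**What the plan says.** All references are to the protocol article.

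- **Attribution claim.** Intervention protocols ends its account of the music phase by saying that the design controls for non-musical factors, "ensuring that the observed effects can be solely attributed to the music intervention".
- **Comparator.** In the same paragraph, MF-nMu and CON golfers "will wear earphones in the same environment but without audio, simply sitting at rest for 15 minutes". Experimental design gives the reason: "Those not receiving the music intervention will sit quietly and rest, a common control in music intervention trials".
- **Arms.** Experimental design has three: Stroop task then music (MF-Mu), Stroop task then rest (MF-nMu), and neither (CON, which reads a magazine and then rests). No arm receives music without the Stroop task.
- **Masking.** The trial "follows a randomized, controlled, partially-blind design". Under Experimental design, "Participants will not be informed of the true purpose of the study", and "testing assistants will be responsible only for recording test results and will not be aware of the participants’ group assignments".
- **Aim.** The last paragraph of the Introduction asks whether music mitigates the harm done by mental fatigue and improves skill performance.
- **Core test.** Statistical analysis makes the three-group, two-time-point time × group interaction the core hypothesis and presents it as verifying the value of music under fatigue. If it is significant, simple effects and Bonferroni-corrected group comparisons follow. No pairwise contrast is singled out as the one for music.

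**The concern.** The attribution sentence is an explicit claim about what the trial can show, and the arms described beside it do not deliver it. Two further features widen the gap. The test offered as verification of music's value compares three groups that also differ in fatigue. And the aim is framed as mitigation of fatigue, although no arm shows what music does to golfers who are not fatigued.

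What is at stake is the conclusion. The Discussion foresees use in training and competition if effectiveness is confirmed. A significant interaction could be read as evidence for music when it shows only that the Stroop task lowered performance. A true MF-Mu versus MF-nMu difference could be credited wholly to music when silence was the alternative and golfers knew which they had.

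**Working it through.** **1. What each pairwise contrast holds constant**

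| Contrast | Fatigue task | Audio phase | What a difference can mean |
|---|---|---|---|
| MF-Mu vs MF-nMu | same (Stroop) | music vs silence | music, any audio effect, expectancy |
| MF-nMu vs CON | Stroop vs magazine | same (silence) | fatigue task |
| MF-Mu vs CON | Stroop vs magazine | music vs silence | both factors together |

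The silent earphones equalise room, duration, posture and earphone wear. They do not equalise sound, or the knowledge that something is being played. Only the first row bears on music, and any expectancy effect lies inside it. Expectancy is not among the listed measures, so the documents give no way to size it.

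**2. The plan's own sample size**

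Inputs (Participants): f = 0.25, α = 0.05, power 0.95, k = 3 groups, m = 2 times, correlation ρ = 0.5, stated N = 66.

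λ = f²·N·m/(1 − ρ) = 0.0625 × 66 × 2/0.5 = 16.5, with df = (k − 1)(m − 1) = 2 and (N − k)(m − 1) = 63.

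Noncentral F power is 0.953. The smallest N reaching 0.95 is 65, which becomes 66 for equal groups. The stated 66 (22 per group) is reproduced.

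**3. Can that test be significant with no music effect?**

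Suppose the Stroop task shifts the mean change by −δ in both fatigue arms and music does nothing. δ is in SDs of the change score; with ρ = 0.5 this SD equals the single-time SD, since √(2(1 − 0.5)) = 1. The mean changes are 0, −δ, −δ, with average −2δ/3. Their squared deviations sum to (4/9 + 1/9 + 1/9)δ² = (2/3)δ², so

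λ = 22 × (2/3)δ² = 14.67δ².

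| Assumed δ | λ | Power of the 2-df interaction, music effect zero |
|---|---|---|
| 0.5 | 3.67 | 0.37 |
| 0.8 | 9.39 | 0.77 |
| 1.0 | 14.67 | 0.93 |
| 1.06 | 16.5 | 0.95 |

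At δ = √(16.5/14.67) = 1.06, fatigue alone gives the full planned power. The protocol states no expected fatigue effect, so the δ values are assumptions shown as a range.

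**4. Power of the contrast that does bear on music**

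This is a two-sample t test on change scores with 22 per arm, 42 df and noncentrality Δ√(22/2). Δ is the assumed MF-Mu versus MF-nMu difference in SDs of change.

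| Assumed Δ | Power, α = 0.05 | Power, α = 0.05/3 |
|---|---|---|
| 0.5 | 0.37 | 0.21 |
| 0.8 | 0.74 | 0.57 |
| 1.0 | 0.90 | 0.79 |

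The 0.05/3 column applies Bonferroni over three pairs. The 0.95 quoted for the interaction does not carry over to this contrast at these values.

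**5. Recovery or general lift**

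If music raised performance by the same amount in rested golfers, MF-Mu would still beat MF-nMu. Telling the two explanations apart needs the effect of music without fatigue, and no arm supplies it.

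**The case against.** **The protocol claims only partial blinding and takes real countermeasures.** This stands in part. Golfers are told that they are at a training camp and should do their best, intervention assistants do not know the objectives, and testing assistants do not know the group. Skill scores count shots landing in a valid area and are verified by a referee, so they are less exposed to expectancy than VAS ratings. A reader might infer that the comparison is wholly unmasked; the documents do not support that. But hiding the purpose does not hide the music, and masked recorders do not govern a golfer's effort or self-ratings. The concealment itself is uncertain, because Participants promises a detailed explanation of the objectives before consent.

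**Quiet rest is a recognised control.** Accepted. Choosing it is not an error. The error is to claim more than it isolates.

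**The missing fourth arm defeats the attribution sentence.** A reader might infer this, but it does not follow. MF-Mu and MF-nMu are randomised and both complete the Stroop task, so attributing their difference to the audio session needs no further arm. The gap limits only the mitigation aim in the Introduction.

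**The follow-up comparisons already reach MF-Mu versus MF-nMu.** True after a significant interaction, and nothing presents MF-Mu versus CON as the music effect. Still, the plan speaks of the interaction as the verification and does not say which comparison carries the conclusion.

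**A gain would be reported as recovery even if fatigue ratings did not differ.** A reader might predict this, but no text says so. VAS-MF is measured, questionnaires are taken before and after the intervention, and the Abstract lists mental fatigue among the primary outcomes. What is absent is a stated link between those ratings and the word recovery.

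**Conclusion.** The concern holds in a limited form. The attribution sentence is wrong as written: the identified effect is 15 minutes of classical music versus silent rest after a Stroop task, including any expectancy or non-specific audio effect, which the masking partly limits. Neither MF-Mu versus CON nor the three-group interaction can by itself support a music effect. With zero music effect and 66 golfers, the interaction is significant with probability 0.37 to 0.93 for assumed fatigue shifts of 0.5 to 1.0 SD of change.

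These figures assume equal shifts in both fatigue arms, ρ = 0.5 and 22 analysed per group. The size of any expectancy effect cannot be estimated from the documents. Separately, reversal of fatigue cannot be distinguished from a general lift in performance. The randomised MF-Mu versus MF-nMu contrast remains valid, and the point does not call for a new arm or a different comparator.

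**What to change.** 1. In Intervention protocols, replace the attribution sentence with the identified effect: 15 minutes of classical music compared with silent rest after a Stroop task. Add that golfers cannot be masked to hearing music.
2. In Statistical analysis, state that the music conclusion rests on the MF-Mu versus MF-nMu difference in pre-to-post change, and not on the omnibus interaction.
3. Use the word recovery only if VAS-MF is also lower in MF-Mu than in MF-nMu, and note that general enhancement cannot be excluded.
4. Optionally, add an expectancy item and report it by arm. It should come only after the skill tests; asked earlier, it could reveal the concealed purpose and prime the expectation it is meant to measure.

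Items 1 to 3 are wording. They change no allocation or measurement and can be made before recruitment, which the article says has not begun. The cost is a narrower headline claim, and one that rests on a contrast with less power than the planned 0.95 across the differences shown above.

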### Measures

This experiment measures multiple variables to comprehensively assess the effects of experimental conditions, including mental fatigue and music intervention, on golf skill performance. The measured variables include mental fatigue, immersion tendency, sport anxiety, attention, motivation, perceived exertion, and golf skill performance (Table 2).

**Table 2 pone.0337905.t002:** Summary of Instruments.

Item	Variable	Instrument	Inventor & Citation	Scale
Independent variable	Mental Fatigue	VAS-MF	Hayes & Patterson, 1921	100 mm scale
Control variables	Immersive Tendency	ITQ	Witmer & Singer, 1998	7-point Liker scale
	Sport Anxiety	SAS-2	Smith et al., 2006	4-point Liker scale
	Attention	SAS-2	Smith et al., 2006	4-point Liker scale
	Motivation	VAS-Mo	Hayes & Patterson, 1921	100 mm scale
	Rating Perception of Effort	Borg RPE	Borg, 1982	15-level scale
Dependent variables	Driving performance	Driving Test	China Golf Association, 2019	10 shots
	Iron performance	150Y Iron Test	China Golf Association, 2019	10 shots
	Chipping performance	30Y Chipping Test	China Golf Association, 2019	10 shots
	Putting performance	Putting Test	China Golf Association, 2019	10 shots

VAS: Visual Analogue Scale; MF: mental fatigue; Mo: motivation; ITQ: Immersive Tendencies Questionnaire; SAS-2: Sport Anxiety Scale-2; Borg RPE: Borg rating of perceived exertion scale; Y: Yard

### Visual analog scale

The Visual Analog Scale (VAS) is used to assess participants’ subjective perception of mental fatigue and task motivation levels [79]. The scoring is based on a 100 mm linear scale, where participants mark a point between 0 (none at all) and 100 (extremely intense) to describe their current level of mental fatigue or motivation.

### Immersive tendency questionnaire

The Immersive Tendency Questionnaire (ITQ) is used to assess participants’ degree of immersion in the virtual environment (music) [80]. This questionnaire consists of 18 items categorized into four factors, including immersive tendency, individual alertness, physical state, and attention-shifting ability. Each item is rated on a 7-point Likert scale, ranging from 1 (strongly disagree) to 7 (strongly agree).

### Sport anxiety scale-2

The Sport Anxiety Scale-2 (SAS-2) assesses participants’ trait sport anxiety levels [81]. This scale consists of 15 items categorized into three factors: somatic anxiety, worry, and concentration disruption. Each item is rated on a 4-point Likert scale, ranging from 1 (not at all) to 4 (very much so).

### Borg rating of perceived exertion

The Borg Rating of Perceived Exertion (Borg RPE) is used to assess individuals’ subjective effort levels [82]. This scale employs a 15-level scoring system, ranging from 6 (extremely easy) to 20 (extremely strenuous), to reflect athletes’ subjective perception of workload intensity during testing, or competition.

### Golf-specific skill tests

The golf-specific skill tests follow the “Golf Skill Level Standards and Testing Methods” established by the China Golf Association [83]. The skill tests include four core skill assessments: driving performance, 150 yards iron shot performance, 30 yards chipping performance, putting performance (Fig 3).

**Fig 3 pone.0337905.g003:**
[figure not shown]
Schematic of site setup and valid zone.

The test venue is set up under the supervision of national-level golf referees from the China Golf Association and certified examiners of the Golf Skill Level Standards and Testing Methods to ensure standardized test conditions. During the testing process, these officials will oversee the entire procedure and make rulings on any disputes related to rules and scores. Practice balls and tees used in the test are provided by the research team. The practice balls are two-piece balls that meet golf equipment regulations, with consistent models and conditions maintained. Participants use their own clubs and gloves to prevent performance variations due to unfamiliar equipment. However, all equipment must comply with the relevant regulations of the Rules of Golf Equipment [84]. The golf referees and examiners on-site will strictly inspect participants’ personal equipment to ensure compliance with regulations. Each skill test requires 10 shots, and the final score is determined by the number of shots that land within the designated valid area. To ensure optimal performance and prevent injuries, all participants will complete a standardized 10-minute warm-up routine led by the head coach before taking the golf-specific skill tests [85,86].

### Data management

All participants signed informed consent forms and voluntarily participated in the experiment. Data management in this study strictly adheres to the General Data Protection Regulation of April 27, 2016, ensuring data confidentiality. The collected data will be used solely for academic research and will not be utilized for any commercial purposes. Participation in this study implies that subjects agree to allow researchers to collect their data and publish the research results in scientific journals. Participants retain the right to access their collected data and may request corrections if errors are found. Additionally, they have the right to withdraw from the study at any time without providing any reason.

All data will be recorded and entered by members of the research team. Psychological measurement data and skill performance data will be documented using paper-based questionnaires and forms. To ensure participant privacy and data security, paper-based data will be entered into the researchers’ electronic database within 24 hours and immediately destroyed. All data will be anonymized using coded identifiers to protect participant identities, with data access restricted to research team members. During data collection, the research team will implement quality control measures, including data integrity checks, cross-checking, and error correction. All electronic data will be regularly backed up, with backup files stored in a cloud storage system. Research findings and data analysis will be made publicly available through peer-reviewed journals or conference presentations.

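### Paper forms, the only original record described, are destroyed as soon as they are keyed, so later entry errors, correction requests and audit queries cannot be settled against source

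*Protocol article*

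**What the plan says.** All statements are in the protocol article.

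- **Medium (Data management).** "Psychological measurement data and skill performance data will be documented using paper-based questionnaires and forms". No scan, photograph, duplicate sheet, double entry or direct electronic capture of these data is described.
- **Fate of the paper (Data management).** Forms go into the "electronic database within 24 hours and immediately destroyed". The stated reason is participant privacy and data security.
- **Quality control (Data management).** "During data collection, the research team will implement quality control measures, including data integrity checks, cross-checking, and error correction". The text does not place any of this between keying and destruction.
- **Participant rights (Data management).** "Participants retain the right to access their collected data and may request corrections if errors are found". No time limit is given.
- **Backups (Data management).** These cover the electronic data.
- **Referee (Experimental design).** "Golf skill test data will be collected on-site by assistant researchers and verified and signed off by a national-level referee to ensure validity".

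**The concern.** Cross-checking and error correction normally mean comparing what was keyed with what was written. The plan promises both, and in the same section removes what was written within about a day. The electronic backups do not fill the gap, because they reproduce whatever was entered, including any mistake.

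The errors that matter most are those inside the permitted range. A count of 7 keyed as 4 passes every range and completeness check, and only the paper would reveal it. The same holds for a visual analogue score that is misread or mistyped but still lies between 0 and 100.

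The skill-test counts feed the accuracy score that the Statistical analysis section names as the single primary outcome. The rule also cannot be undone: an analysis choice can be revisited once the data are in, but a destroyed form cannot be recovered.

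**Working it through.** The point does not depend on alpha, power, effect size or sample size, and the plan gives no figure to reproduce. The check is a comparison of statements, followed by a rough size.

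**1. Order of events**

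| Step | When, according to the article | Needs the paper? | Still possible after destruction? |
|---|---|---|---|
| Referee verifies and signs scores | On site, at testing | Yes | Already done; the signed record is lost |
| Keying into the database | Within 24 hours | Yes | Already done |
| Check of entries against paper | Not placed anywhere | Yes | No |
| Range and completeness checks | During data collection | No | Yes |
| Participant asks for a correction | No limit stated | To verify the value, yes | The request yes, verification no |
| Audit or query at data cleaning | Not described | Yes | No |

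The Status and timeline section expects data collection to end by 30 November 2025 and analysis to finish by 31 December 2025. With a 24-hour limit, the last forms would be gone by about 1 December. Any query raised while the final data set is being cleaned or analysed would then have no source.

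**2. Number of shot counts at risk**

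Inputs: 76 golfers to be recruited (Participants); 2 time points (Statistical analysis); 4 skill tests (Golf-specific skill tests).

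76 × 2 × 4 = 608 counts.

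The article gives no entry error rate. Assuming 0.5–1%:

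- 608 × 0.005 = 3.04
- 608 × 0.01 = 6.08

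That is about 3–6 wrong counts, on the further assumption that none is caught before the paper is destroyed. Questionnaire and visual analogue forms come on top and are not counted here.

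**3. Size of one error**

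Each test is scored as the number of valid shots out of 10. A one-shot slip therefore changes that participant's score on that test by 1/10 of its range. In a group mean the same slip amounts to 1/22 = 0.05 shots with the 22 per group of the sample-size calculation, or 1/25 = 0.04 shots with about 25 per group (76/3 ≈ 25). The article gives no standard deviation for shot counts, so these shifts cannot be turned into a loss of power.

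**4. If the doubtful values were set to missing**

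3/608 = 0.5% and 6/608 = 1.0%. Both lie well under the 5% that the Statistical analysis section gives as its example of a high proportion of missing data, above which multiple imputation is used. This cause alone would not reach it.

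**The case against.** Several objections are sound and limit the point.

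- **The referee's check is not prevented.** A reader might infer that destroying the sheets defeats referee verification. It does not: collection, verification and sign-off take place on site, before entry. What is lost is the later proof that the database agrees with what was signed.
- **Quality control is not ruled out.** The article places these measures during data collection, and a comparison with paper at the moment of keying would be consistent with the text. Electronic range and completeness checks can run at any time. One might also say that the order of checking belongs in the full protocol. That is fair for the order, but the destruction rule is stated here and is not an omission.
- **Participants keep their rights.** They can still see their data and ask for changes. Only the means of verifying a disputed value disappears.
- **The harm is modest.** A large slip, such as 1 keyed for 10, would move a group mean by 9/22 = 0.41 shots, or 9/25 = 0.36 with about 25 per group. That is a worst case and no guide to the expected effect. Nor do the documents support a claim of bias: no mechanism would make keying errors favour one group, and those recording the skill tests are to be unaware of allocation.

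What stands is narrower. No check against paper is stated before destruction, and none is possible afterwards.

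**Conclusion.** The point holds in limited form. The plan fixes an irreversible destruction of the only original record it describes, and this weakens its own commitment to cross-checking and error correction. The consequence is noise that cannot be corrected and results that cannot be traced to source.

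On an assumed 0.5–1% error rate, with nothing caught before destruction, about 3–6 of 608 shot counts would be affected, most plausibly at random across groups. If same-day checking against paper is in fact done, the number is smaller, but the loss of the audit trail is unchanged.

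Nothing here shows a threat to the primary conclusion, and no test, sample size or outcome definition is touched. The change should be made because it is cheap and cannot be made later, but the trial's validity does not hinge on it.

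**What to change.** In Data management, replace immediate destruction with a retention rule along these lines: coded questionnaires and referee-signed score sheets, or scans verified against them, are kept in secure storage, with the key linking codes to identities held separately. They are kept until entries have been checked against source and the database is locked, and are then disposed of under the institution's retention rule. The section should also state when the check against source takes place.

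The privacy aim is still met, since coded identifiers and access restricted to the research team are already planned. The cost is secure storage, a somewhat longer holding of coded paper and the time for the check. The Status and timeline section reports that neither recruitment nor data collection had begun, so on that status the change could be in place before the first form is completed.
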